# Safety assurance

## Safety of the procedure

Apart from the invasiveness of the procedure (there is the need for a big central venous access that most critical patients need anyway) the method is known to be safe. (12, 13) (15) Possible complications associated with the implementation of the central venous access are bleeding, infection, malpuncture including arterial malpuncture, damage to surrounding organs including lung injuries requiring drainage, thromboses, embolisms and in very rare cases strokes. Rarely allergic reactions to the system are described, (17) which would lead to immediate disruption of the therapy and adequate antiallergic therapy. There is the need for anticoagulation (PTT aim 60-80), which is usually done with Heparine. Heparin induced thrombocytopenia (HIT) is a known adverse events associated with heparin. In suspected or proven HIT patients heparin will be stopped immediately. Alternative anticoagulation (citrate or Argatroban) can be used. For patients with increased risk of bleeding citrate anticoagulation is possible. Since it cannot be excluded that drugs, including antibiotics, are partially removed by the filter, patients receiving antibiotic therapy receive an additional antibiotic dosage after each filter change to avoid underdosage.

## Risk mitigation

The implementation of the central venous catheter is only done by experienced doctors and with ultrasound control. If the patient is receiving antibiotics an additional dose is given after every filter exchange in order to control for underdosage.

## Safety assessment

CytoSorb is a medical device which is already well implemented in routine clinical practice and CE-certified in the European Union. Several clinical studies and also a large registry have not shown any serious side effects. It can be assumed that this can also be transferred to the study participants. The medical device is used within the scope of its approval.

However, in order to exclude risks for the study participants a safety surveillance system will be established and will follow the applicable legislation, standards and SOPs of the CSC Charité. Treating physician visits all patients at least twice a day and any adverse event is documented in the patient file as well as in the eCRF of the electronic database and assessed by the investigators for seriousness. SAE will be sent within 24 hours to the sponsor/medical monitor of the trial. A data safety monitoring board (DSMB) with three external reviewers will review the safety during the trial. It is proposed that the DSMB will meet at regular intervals (after every 10 patients included in each randomization group) via videoconference after start of the trial, to review the safety data of the study. Moreover, members of the DMSB will be informed about adverse events every 2 weeks in between the meetings or immediately in case of the occurrence of unexpected events. In addition, members of the DMSB will be informed on the progress of the trial (in particular recruitment and dropout rate) and will give written recommendations to the funding organization if the study should be discontinued. After the inclusion of 10 patients in each randomization group a report is given to the local ethics committee of the Charité.

## Criteria for Study discontinuation

Stopping rules for the individual patient is patient wish, adverse event (e.g. allergic reaction to CytoSorb, contraindication for anticoagulation, severe thrombocytopenia (<20000/ /μl) or proven bacterial infection during treatment course as we want to see the effect of CytoSorb on suspected cytokine storm and distinguish from other effects leading to vasoplegic shock such as sepsis.

As CytoSorb is already part of routine clinical practice and well known to the users and because of the short trial duration of 8 weeks we did not put restrictions on inclusion rates for each participating site.

Stopping rules for the whole trial are safety concerns due to the ongoing surveillance of mortality and adverse events by investigators as well as the DSMB. Furthermore, an interim analysis of the data is done after the inclusion of 10 patients in each group and a new consultation of the ethics committee is mandatory.

# Data management

Routine clinical data are continuously documented in the patient file. Due to the acute situation and pragmatic study design data collection is restricted to the most important clinical outcome variables. The personal data such as name and date of birth will only be accessible to the attending physician. All protocol‐required information collected during the trial will be documented in an electronic case report form (eCRF) by the investigator, or a designated representative. Data capture and data management will be performed using electronic case report forms (eCRF) based on the study software secuTrial^®^ which is provided by the Clinical Study Center (CSC) Charité. secuTrial^®^ features remote web based data capture and performs authentication procedures, role management, query management and encrypted and secured connections. The data will only be hosted within the Charité IT infrastructure. All modification in the eCRF will be documented by an internal audit trail. Data will be captured shortly after source data documentation and reviewed by programmed plausibility-checks to assure the quality of the data. After the end of the study all data will be exported in an appropriate format and tested by SAS for plausibility and consistency. The database will be closed after accomplished data cleaning. Electronic documentation includes all exported files, SAS scripts, data protocol and the closed database. The participant’s data will be saved and transferred in pseudonymous form. All regulative requirements applying to data protection will be met. Re-identification of a participant’s name is only possible at the study site. The results of the above-mentioned study, compiled according to groups, will be published in a medical journal without the possibility of reference to the respective person and regardless of whether the results are positive or negative. The data recorded outside the medical record will be destroyed by the end of the study.

# Statistical analysis

A recent retrospective observational study showed a mortality of 61.5% in a cohort of 52 critically ill COVID-19 patients. (18) Due to both the explorative character of the study (new virus, heterogeneous data on efficacy of CytoSorb-treatment in general an no data in COVID-19-patients at all) and few data on possible recruiting rates (patient flow not estimable, patient condition not estimable) we cannot make assumptions on the effect size of the intervention. That is why, supported by the Institute of Biometry and Clinical Epidemiology of the Charité, we decided on an investigator-initiated clinical pilotstudy in order to evaluate the feasibility of recruitment and gain knowledge concerning the intervention effect. We will consecutively include all eligible patients for a period of eight weeks and randomize them to either receive CytoSorb treatment or standard of care without CytoSorb in order to plan an adequately powered randomized controlled trial with the gained knowledge on effect size and recruitment feasibility as a subsequent trial.

The primary analysis in order to evaluate the effect of the intervention will be carried out with a shared frailty model with time until resolution of vasoplegic shock as outcome variable censored at the time of death. The randomization group will be included as fixed effect and additionally possible confounder such as age, sex and pre-existing illness.

The intensive care unit where the patient is treated will be added as random effect in the model in order to control for cluster effects.

As an additional analysis, death will be treated as competing risk, results will be shown in a cumulative incidence function.

Secondary endpoints will be evaluated with adequate models (proportional hazards model / ANCOVA / logistic regression) depending on distribution of endpoint variables.

All the analyses will be explorative and will not be controlled for multiple testing. Since missing data is not expected, imputation is not planned.

Blinding of the investigator and patient is not possible as a clinical intervention is done, statistician will receive a blinded data set, so that all analyses will be conducted blinded.

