## Sample size

Not applicable as the study serves as a pilotstudy. Possibly 85-100 patients

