# Study design

Multicenter, prospective, open-label, randomized pilotstudy investigating the effect of the use of CytoSorb in patients with vasoplegic shock due to suspected cytokine storm in patients with COVID-19. We will consecutively include all eligible patients during a timeframe of eight weeks and randomize them to receive either CytoSorb treatment or standard of care without CytoSorb to eventually plan an adequately powered randomized controlled trial with sample size calculation as a subsequent trial. Study centers will be approximately 5 sites in Germany with approximately 10 Intensive Care Units (ICU). We are assuming an inclusion rate of possibly 85-100 patients.

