# Study assessment

All laboratory determinations including will be analyzed locally.

Baseline variables:

- Age
- Sex
- Smoker status
- Comorbidities
  - Hypertension
  - Diabetes
  - Coronary heart disease
  - COPD
  - History of malignancy
  - Chronic kidney disease
  - Immunosuppression
  - Other

At inclusion

- Oxygen supplementation
- NIV/High Flow
- Intubation
- ECMO
- Vasoplegic shock
- Dose of Noradrenaline
- Other Vasopressors
- Glucocorticoids
- Antiviral treatment
- SOFA
- APACHE

Outcome parameters

- Time to resolution of shock (d)
- Need for mechanical ventilation
- Days on ventilator after inclusion (d)
- ICU survival
- In-hospital mortality
- 7 day mortality
- Septic shock
- Cardiogenic shock
- Acute kidney injury after Inclusion (AKIN-Stage 1,2,3)
- Dialysis
- Duration of ICU stay
- Vasopressor dose (max) on day 1
- Vasopressor dose (max) on day 2
- Vasopressor dose (max) on day 3
- Change to palliative therapy

Adverse events

- technical failure
- mashine clotting
- other

Serious adverse events

- Cardiac arrest
- Severe bleeding
- Severe allergic reaction
- Severe Complication due to shaldon catheter insertion
- Death
- Other

Complication possibly associated with CytoSorb

- Heparin induced thrombycytopenia Type 2 (HIT 2) if heparine is exclusively needed for CytoSorb therapy
- Complication associated with shaldon catheter insertion if catheter is exclusively needed for CytoSorb therapy
- Severe allergic reaction associated with CytoSorb therapy
- Other

Laboratory Data (day 1+3+7)

- CRP
- Troponin
- D-Dimer
- IL-6 (Only Day 1+3)
- Ferritin
- LDH
- Creatinine
- ALT
- PCT
- Phosphate

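### The primary frailty model names age, sex and pre-existing illness as example covariates but no measure of shock severity, although noradrenaline dose and SOFA are recorded at inclusion

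*Protocol*

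**What the plan says.** The Statistical analysis section of the protocol specifies a "shared frailty model with time until resolution of vasoplegic shock as outcome variable censored at the time of death". On fixed effects it says: "The randomization group will be included as fixed effect and additionally possible confounder such as age, sex and pre-existing illness". ICU enters as a random effect. The coding of pre-existing illness is not given, and the wording makes the named covariates examples rather than a complete list.

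The Study assessment section lists "Dose of Noradrenaline", SOFA and APACHE among the items recorded at inclusion, and eight comorbidity items among the baseline variables. Under Study Endpoints, resolution means no need for vasopressors for at least 8 hours. The inclusion criteria require noradrenaline above 0.2 µg/min/kg and set no upper limit. The Randomization section names no stratification factor.

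No effect size is assumed: "we cannot make assumptions on the effect size of the intervention". The role of the analysis is stated as: "All the analyses will be explorative and will not be controlled for multiple testing".

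**The concern.** Starting noradrenaline dose is the entry value of the quantity whose disappearance defines the primary endpoint. It can vary widely above the entry threshold, and nothing stated in the randomisation balances it. It is therefore the first candidate for adjustment, with SOFA close behind. The protocol names other variables and justifies them as possible confounders. In a randomised trial that is not the reason to adjust; the reason is prognostic strength.

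The pilot is meant to supply an effect size for the trial that follows. An estimate that ignores a strong predictor has less power, moves with any chance difference in starting dose between the arms, and lies nearer to 1 than the HR conditional on severity. A second issue is that pre-existing illness could be spread over many terms while resolution events may be few.

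**Working it through.** **The plan's own figure.** There is none to reproduce. The sample size section reads "Not applicable as the study serves as a pilotstudy. Possibly 85-100 patients", and Study design repeats this as an expectation: "We are assuming an inclusion rate of possibly 85-100 patients". Alpha, power, effect size and number of events are not stated.

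**Events (assumption).** The only event rate in the document is background: "A recent retrospective observational study showed a mortality of 61.5% in a cohort of 52 critically ill COVID-19 patients". If that share died before resolution and every survivor resolved, events = N × (1 − 0.615):
- N = 85: 85 × 0.385 = 32.7
- N = 100: 100 × 0.385 = 38.5

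That is about 33 to 38 events. If 40% die unresolved: 85 × 0.6 = 51 to 100 × 0.6 = 60. If 20%: 85 × 0.8 = 68 to 100 × 0.8 = 80.

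**Fixed parameters.** One illness term: group + age + sex + illness = 4. Eight separate terms: 1 + 1 + 1 + 8 = 11, which is the maximum coding of the named covariates.

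| Share dying unresolved | Events | Events per parameter, 4 | Events per parameter, 11 |
|---|---|---|---|
| 61.5% | 33–38 | 8.2–9.6 | 3.0–3.5 |
| 40% | 51–60 | 12.8–15 | 4.6–5.5 |
| 20% | 68–80 | 17–20 | 6.2–7.3 |

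**What severity adjustment is worth.** Cox simulation, 2,000 runs per setting. Assumptions:
- 1:1 allocation (the ratio is not stated) and no ICU frailty
- death as censoring, with severity also raising the death hazard
- 0.4 log-hazard of resolution per SD for each of dose and SOFA, correlation 0.5
- 0.2 per SD for age; sex and comorbidities without effect

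Taken together, dose and SOFA then carry 0.4 × √(1 + 1 + 2 × 0.5) = 0.69 on the log-hazard scale, which is a strong predictor. Mean events were about 35 (N = 85) and 40 (N = 100). Each cell gives N = 85 / N = 100.

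| Model | Fixed parameters | Power, HR 2 | Median HR (true 2) | Rejection under no effect, nominal 5% |
|---|---|---|---|---|
| Group only | 1 | 0.386 / 0.441 | 1.81 / 1.80 | 0.054 / 0.045 |
| Group, age, sex, one illness term | 4 | 0.384 / 0.440 | 1.86 / 1.85 | 0.062 / 0.048 |
| Group, age, sex, eight illness terms | 11 | 0.400 / 0.465 | 1.98 / 1.99 | 0.087 / 0.065 |
| Group, dose, SOFA | 3 | 0.476 / 0.533 | 2.02 / 2.00 | 0.061 / 0.051 |
| Group, age, sex, one illness term, dose, SOFA | 6 | 0.485 / 0.545 | 2.12 / 2.09 | 0.074 / 0.056 |

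Against the 4-parameter model, dose and SOFA add 0.476 − 0.384 = 0.092 and 0.533 − 0.440 = 0.093. Monte Carlo error is about √(0.25/2000) = 0.011 per cell.

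The median standard error of the log HR is the same in both models (0.372 at N = 85, 0.342 at N = 100). The gain therefore comes from removing the pull toward 1, not from a smaller standard error. The 11-parameter model's median near 2 does not show that it recovers severity. Overfitting pushes the estimate outward and offsets the attenuation, while its spread is larger (0.460 against 0.376 at N = 85).

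**Sensitivity to prognostic strength and events.** Separate simulations used n = 92, baseline dose as the only predictor, and true HR 2. At 0.7 per SD, power was 60% adjusting for dose and 49% unadjusted. At 0.4 per SD it was 58% against 54%. With about 75 events and 0.4 to 0.7 per SD, power was 83–85% adjusting for dose against 64–76% with the 4-parameter model.

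**Chance imbalance.** With 46 per arm, the difference in mean dose has SD √(2/46) = 0.209 SD units, so a gap of at least 0.2 SD arises in about 34% of trials. A gap of 0.2 SD moves the unadjusted HR by a factor of exp(0.2 × 0.4) = 1.08 to exp(0.2 × 0.7) = 1.15.

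**The case against.** Several points on the other side are sound.

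- A reader might infer that the plan excludes severity. It does not: the covariates are given as examples, so dose and SOFA are unnamed rather than ruled out.
- The Data Sharing Statement refers to a separate statistical analysis plan, which is not at hand. The coding of pre-existing illness and the final list may be settled there.
- A reader might infer that the primary comparison is confounded. Randomisation removes that in expectation, and the pull toward 1 is the known gap between an HR that averages over severity and one conditional on it, not an invalid analysis.
- A reader might infer that 11 parameters will be fitted to 33 to 38 events. Neither number is in the protocol. Eleven is the maximum coding, and the event count borrows the mortality of an external cohort. Patients who resolve and later die still count as events, which would raise it; unresolved survivors would lower it.
- The trial is exploratory, with no alpha or power target, so it cannot be said to miss one. The statistician works on a blinded data set, which limits data-driven choice of covariates.

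What remains is that the protocol does name covariates for its primary model and leaves out the most obvious one it collects. The gain appears against the 4-parameter model too, and does not vanish with more events. Neither blinding nor an unseen analysis plan alters which covariates this document names.

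**Conclusion.** The point holds in a limited form. The protocol's named covariates include no severity measure, although two suitable ones are recorded at inclusion and one is tied directly to the endpoint. The comparison is not biased in expectation. The cost is lower power, unadjusted chance imbalance in starting dose, and an HR nearer to 1 than the severity-conditional one.

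Under the stated assumptions (true HR 2, 0.4 log-hazard per SD for each of dose and SOFA), the cost is about 9 percentage points of power, with a median HR of about 1.85 instead of about 2.0. If dose alone were prognostic at 0.4 per SD, it falls to about 4 points against an unadjusted analysis. The documents give no prognostic strength, so the size is illustrative and only the direction is firm. The parameter count is a secondary concern: it becomes serious only if pre-existing illness is split into eight terms and events are near the low end of the 33 to 80 range.

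**What to change.** In the Statistical analysis section, replace the open list with a fixed one: randomisation group, log baseline noradrenaline dose, SOFA and age as fixed effects, with ICU as random effect. Enter pre-existing illness as at most one term, or move it together with sex to a sensitivity analysis.

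The proposed model has 4 fixed parameters, the same as the named covariates with one illness term, so events per parameter stay at 8.2 to 9.6 even at 61.5% dying unresolved. Adding one illness term makes 5, or 32.7/5 = 6.5 to 38.5/5 = 7.7. The exact proposed set was not simulated. The 3- and 6-parameter severity models bracket it in size, and the larger one overshoots slightly (median HR 2.09 to 2.12), which is a reason to keep the list short.

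The change costs one or two sentences, and every variable is already collected. The HR becomes conditional on severity and must be reported as such when the next trial is planned. One or two degrees of freedom go to dose and SOFA.

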### Secondary Endpoints:

- 7 day mortality after fulfilling the inclusion criteria
- mortality until hospital discharge
- measurement of IL-6 on day 1 and 3 of intervention
- need for mechanical ventilation
- duration of mechanical ventilation
- duration of ICU-stay
- catecholamine dose on day 1/2/3 after start of CytoSorb
- acute kidney injury

As primary endpoint we decided on the time until resolution of vasoplegic shock, a well implemented, clinically relevant endpoint in critical care. Two big intensive care studies already used this endpoint as secondary endpoint. (8, 9)

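### The protocol assumes no missing data, but early death and withdrawn consent remove secondary-endpoint values, and without a rule for death these endpoints can favour the arm with more deaths

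*Protocol*

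**What the plan says.** The protocol's Statistical analysis section makes a definite statement about missing values: "Since missing data is not expected, imputation is not planned". It opens with an outside figure: "A recent retrospective observational study showed a mortality of 61.5% in a cohort of 52 critically ill COVID-19 patients".

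For the primary endpoint, death is handled twice: times are censored at death in the frailty model, and an additional analysis treats death as a competing risk with a cumulative incidence function. For the secondary endpoints the section says only: "Secondary endpoints will be evaluated with adequate models (proportional hazards model / ANCOVA / logistic regression) depending on distribution of endpoint variables".

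Four of the eight secondary endpoints are exposed to death, in whole or in part: "duration of mechanical ventilation", "duration of ICU-stay", "catecholamine dose on day 1/2/3 after start of CytoSorb", and IL-6 on days 1 and 3. Study assessment records the dose as a daily maximum (for example "Vasopressor dose (max) on day 3") and ventilation as days after inclusion, with no entry for patients who have died. Informed consent adds that a patient who refuses consent afterwards has the data discarded. The Sample size entry reads "Not applicable as the study serves as a pilotstudy. Possibly 85-100 patients".

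**The concern.** The statement does not fit the trial's own setting. Patients enter in vasopressor-dependent shock, 7-day mortality is itself an endpoint, and one consent route leads to loss of data. Some patients will have no day-3 dose or IL-6 value.

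The second difficulty is the criterion for choosing a secondary model. The shape of the distribution does not settle how a death enters. An ANCOVA on observed values compares only patients alive to be measured. If sicker patients die first, the arm with more early deaths is left with the less sick. A raw duration ending at death records an early death as a short ventilation or ICU stay.

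The pilot is meant to supply knowledge of effect size for a larger trial. Secondary results that improve as mortality rises could mislead that planning.

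**Working it through.** The protocol gives no figure for missing data or early death, so there is nothing of its own to reproduce beyond the cited mortality: 32/52 = 61.5%. Everything below is illustration under stated assumptions.

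**1. How many values could early death remove?** Assume, for illustration only, that 61.5% mortality applies, accrues at a constant hazard and is reached at horizon H (the protocol states none). Then P(dead by day t) = 1 − (1 − 0.615)^(t/H).

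| Assumed H | Dead by day 2 | Dead by day 3 | Day-3 count, N = 85 to 100 |
|---|---|---|---|
| 14 days | 12.7% | 18.5% | 15.7 to 18.5 |
| 28 days | 6.6% | 9.7% | 8.3 to 9.7 |
| 60 days | 3.1% | 4.7% | 4.0 to 4.7 |

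This is roughly 4 to 19 patients by day 3.

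**2. Bias in dose, upper end.** Let dose be standard normal with no treatment effect, and let the fraction q who die early be exactly the highest-dose patients. The mean among the rest is −φ(z)/(1 − q), where z is the (1 − q) quantile.

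- q = 5%: −0.109
- q = 15%: −0.274
- Difference: 0.274 − 0.109 = 0.165 from rounded values (0.166 unrounded), or about 0.17 SD lower in the arm with more deaths.

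**3. Bias in dose, weaker link.** If dose has correlation r with the risk that determines early death, the shift is r × 0.166: 0.05 SD at r = 0.3 and 0.08 SD at r = 0.5.

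A simulation with lognormal dose (assumed median 0.35; log-scale SD √(0.6² + 0.3²) = 0.67), a logistic risk of death and no treatment effect agrees. Geometric mean observed day-3 dose is 0.340 with 5% dead and 0.324 with 15% dead. The shift is ln(0.340/0.324)/0.67 ≈ 0.07 SD. Day-3 IL-6 would move the same way if high IL-6 goes with early death.

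**4. Duration of ICU stay.** Assume constant hazards, the same discharge-alive hazard of 0.0275 per day in both arms, and ICU mortality m of 70% vs 55%. Mean stay is 1/(h_death + h_discharge) = (1 − m)/0.0275.

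| Analysis | 70% arm | 55% arm | Reading |
|---|---|---|---|
| Raw mean stay | 0.30/0.0275 = 10.9 days | 0.45/0.0275 = 16.4 days | Worse arm looks 5.5 days better |
| Any end of stay as event | | | HR 0.45/0.30 = 1.50, shorter stay in the worse arm |
| Deaths censored | | | Cause-specific HR for discharge alive 1.0 |
| Death as competing event | 30% discharged alive | 45% discharged alive | Correct direction |

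The listed model families therefore do not settle the answer. A proportional hazards model gives 1.50 or 1.0 depending on how death is coded.

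A simpler bound for ventilation: if survivors are ventilated 5 to 15 days longer than non-survivors (assumption), 10 points more mortality shortens the mean by 0.10 × 5 = 0.5 to 0.10 × 15 = 1.5 days.

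**The case against.** The strongest reply is that the model and death rule for each secondary endpoint normally belong in the statistical analysis plan, which the Data Sharing Statement mentions and which is not at hand. That is right as far as a missing rule goes. It does not cover what the protocol does state: a premise that missing data will not occur, and distribution as the basis for choosing the model. An analysis plan written to follow the protocol would inherit both.

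It can also be said that a dose after death is undefined rather than missing, so the sentence may refer only to data capture from routine ICU records. This stands in part. Imputation is not the remedy, and the sentence does not itself cause the problem with durations. But data discarded after refusal are missing on any reading.

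Several stronger readings are tempting and are not supported:

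- **That the trial expects 61.5% mortality.** The figure belongs to an outside cohort of 52 and has no time horizon. Only deaths by day 3 affect dose and IL-6, and the protocol gives no figure for those.
- **That ANCOVA on survivors is the plan.** It is one of three listed families, and none is assigned to an endpoint. Proportional hazards with deaths censored would remove the false advantage in durations, but the protocol does not commit to it.
- **That four endpoints are wholly lost to death.** Day-1 dose and IL-6 are largely unaffected, and a patient who dies on day 2 still has a day-2 maximum.
- **That 0.17 SD is the likely bias.** It assumes perfect correlation, and 15% vs 5% implies a hazard ratio of ln 0.85/ln 0.95 ≈ 3.2. The standard error of a mean difference with 85 to 100 patients is about 2/√N = 0.20 to 0.22 SD, so even the upper end is below one standard error.

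Mortality is also reported separately, which helps a reader notice a conflict between endpoints.

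**Conclusion.** The point holds in a limited form. The no-missing-data premise conflicts with the clinical setting the protocol describes and with its own consent procedure. With the model chosen by distribution alone, nothing stops day-2/3 dose, day-3 IL-6, ventilation duration and ICU stay from favouring the arm with more deaths.

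This can happen only if mortality differs between arms. For dose and IL-6 it further requires that sicker patients die earlier; for durations it requires an analysis that counts death as the end of the duration. The size for dose is at most about 0.17 SD in the 15% vs 5% scenario, more plausibly 0.05 to 0.08 SD. For ICU stay it can reach several days under a 15-point mortality difference. All of these rest on assumed hazards, horizons and correlations.

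The primary endpoint is not touched by this point, and all analyses are declared exploratory. The change is worth making because the pilot is to inform the next trial, but the trial does not depend on it.

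**What to change.** 1. Delete the statement that missing data are not expected. Report missing values by arm and reason, separating death from refused consent and other causes.
2. Analyse ventilation and ICU duration as time to liberation from the ventilator or discharge alive, with death as a competing event. This extends the method already planned for the primary endpoint. Ventilator-free and ICU-free days with death set to 0 are an alternative if the eCRF holds the necessary dates and status.
3. For day-2/3 vasopressor dose and day-3 IL-6, use a rank-based comparison with prior death as the worst rank. Show the observed-value ANCOVA as descriptive.

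Cost: items 1 and 3 are mainly analysis wording. For item 2, the sponsor should confirm that times of ventilator liberation, ICU discharge and death are recorded, because Study assessment lists durations and outcomes rather than dates. A reader might take free days to day 28 as a free substitute, but the listed items do not include day-28 status after discharge, and replacing two endpoints is an endpoint change. Rank-based and competing-risk effects are somewhat less direct to read than a difference in means.
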